### Confounder variables and effect modifiers

Factors, which interfere with outcome measures, can distort the results if unevenly distributed between study groups. We use three approaches to control for confounders: First, we use randomisation to allocate patients. Second, we strengthen the randomisation using a computerised minimisation procedure with factors that are likely to influence the outcome measures (exercise capacity, pulmonary state and presence and absence of affective disorders). Third, we will collect a number of variables at baseline (age, gender, lung function, time since diagnosis, cumulative dose of oral steroids in previous three months, medication, cardiovascular, musculoskelettal and endocrine co-morbidities) that may modify the effect of exercise. We will compare the distribution of these potential effect modifiers between groups and statistically assess their influence on the outcome measures with multiple linear regression models.

#### Sample size

For calculating the required sample size, we use the formula for comparison of 2 means: n = [A + B]^2 ^* 2 * SD^2^/DIFF^2^, where n = the sample size required in each group (double for total sample), SD = standard deviation of the outcome variable, DIFF = size of desired difference between groups. A and B depend on the desired significance level and desired power, respectively.

We base our sample size calculations on the CRQ. We used empirical data from our previous trial.[27], where we applied similar inclusion criteria for patients with COPD undergoing respiratory rehabilitation, to estimate variability of the CRQ (standard deviation of the CRQ domain scores between 0.8 and 1.2). A clinically sensible way to determine the size of desired difference between groups (DIFF in formula above) is based on the minimal important difference (0.5 on the scale from 1 to 7 for the CRQ)[41-43,48] A sample size of 44 patients in each group will allow showing a difference of 0.5 in CRQ scores between the groups, assuming a standard deviation of 0.8, with a power of 90% at a significance level of 5% (one-sided). Assuming a drop out rate of 15%.[27], the total minimal sample size increases to 104. This sample size will also allow detecting a difference of 45 meters in the six-minute walking test scores between the two treatment groups with a power of 95% at a significance level of 5% (one-sided) assuming a drop out rate of 15%.

A priori sample size calculations usually provide only rough estimates. Therefore, we will recalculate sample size during the study when we have the data for 30 patients in each group. To this end, we will re-assess the standard deviation of the outcome variables and, if necessary, adjust the sample size accordingly (without breaking the randomisation code).

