### Effectiveness

Our null hypothesis is that high intensity continuous exercise is of clinically superior effectiveness compared with interval exercise to improve HRQL (δ ≥ 0.5 in CRQ domains scores). The alternative hypothesis is that interval exercise is not of clinically inferior effectiveness compared with high intensity continuous exercise.

In the primary analysis, we will calculate the raw difference and 95% confidence intervals between groups in the mean follow-up score for the CRQ domains 2 weeks after completion of the respiratory rehabilitation programme. In an additional analysis, we will adjust for the base-line score and the four stratification variables using an analysis of covariance. We will use independent t-test to compare the change scores between groups.

We will also use the confidence interval approach as recommended for equivalence and non-inferiority trials[13] We will establish non-inferiority of interval exercise if the point estimate and its 95% confidence interval for difference between the change scores of the continuous and interval exercise group is smaller than the a priori determined boundary of clinical equivalence (see figure 3). If the 95% confidence intervals lie outside the boundaries of clinical equivalence we will establish clinical superiority of one exercise protocol.

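### The initial sample size of 104 gives the stated 90% power only at an SD of 0.8, the lowest value in the plan's own range of 0.8 to 1.2 for CRQ domain scores

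*Protocol article*

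**What the plan says.** The Sample size section of the protocol article draws its variability from the investigators' earlier trial in similar patients and gives a "standard deviation of the CRQ domain scores between 0.8 and 1.2". It then fixes one value: "A sample size of 44 patients in each group will allow showing a difference of 0.5 in CRQ scores between the groups". That claim is made for an SD of 0.8, 90% power and a one-sided 5% level. The formula is for a comparison of two means, with "n = the sample size required in each group (double for total sample"). After allowance for 15% drop-out, "the total minimal sample size increases to 104". No reason is given for planning at 0.8.

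The Effectiveness section sets the null hypothesis at "δ ≥ 0.5 in CRQ domains scores". Its primary analysis compares the groups on the CRQ domains two weeks after rehabilitation, and no single domain is named as primary. The decision rule is a confidence interval: "We will establish non-inferiority of interval exercise if the point estimate and its 95% confidence interval for difference between the change scores" stays below the boundary of clinical equivalence.

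The Sample size section also describes a priori calculations as rough. Once data are available for 30 patients per group, and with the randomisation code unbroken, "we will re-assess the standard deviation of the outcome variables and, if necessary, adjust the sample size accordingly". It does not say which domain's SD governs that step.

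**The concern.** The plan's own range shows that at least one CRQ domain had an SD well above 0.8, yet the trial is sized for the most favourable end. The hypothesis is framed over the domains generally and the 90% is attached to CRQ scores without naming a domain. A reader would therefore take 90% as the chance of showing non-inferiority on whichever domain is examined. For a domain with a larger SD the chance is lower.

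In a non-inferiority trial, the consequence of low power is an inconclusive interval. The Background section makes this criticism of the earlier trials, which it considers too small to show equivalence or non-inferiority.

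**Working it through.** **Inputs.** Margin 0.5 (Effectiveness; Sample size). 44 evaluable per group, 1:1 allocation, SD range 0.8 to 1.2, one-sided 5%, 15% drop-out (Sample size). 95% confidence interval for the decision (Effectiveness), read as two-sided and so equivalent to one-sided 2.5%. A true difference of 0 is my assumption; the plan does not state one.

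**The plan's own figure.** n = (A + B)² × 2 × SD² / DIFF². With A = 1.645 (one-sided 5%), B = 1.282 (90% power), SD 0.8 and DIFF 0.5:

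(1.645 + 1.282)² × 2 × 0.64 / 0.25 = 43.9, rounded up to 44 per group.

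Drop-out: 88 / 0.85 = 103.5, rounded up to 104. Both stated figures reproduce.

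**Power at other SDs in the plan's range, 44 evaluable per group.** Power = Φ(0.5 / (SD × √(2/44)) − z), with √(2/44) = 0.2132, and z = 1.645 for one-sided 5% or 1.960 for the 95% interval.

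- SD 0.8: 0.5 / 0.1706 = 2.931
- SD 1.0: 0.5 / 0.2132 = 2.345
- SD 1.2: 0.5 / 0.2558 = 1.954

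| SD | One-sided 5% | 95% interval |
|---|---|---|
| 0.8 | 90.1% | 83.4% |
| 0.9 | 83.2% | 74.1% |
| 1.0 | 75.8% | 65.0% |
| 1.1 | 68.7% | 56.8% |
| 1.2 | 62.2% | 49.8% |

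The noncentral t distribution gives nearly the same values (at SD 1.2, 61.6% and 48.9%). If nobody dropped out (52 per group), SD 1.2 would still give only 68.4% and 56.5%, so the drop-out allowance does not close the gap.

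**Size needed for 90% power.**

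- SD 1.0, one-sided 5%: 8.564 × 2 × 1.00 / 0.25 = 68.5, so 69 per group; 138 / 0.85 gives 163 in total.
- SD 1.2, one-sided 5%: 8.564 × 2 × 1.44 / 0.25 = 98.7, so 99 per group; 198 / 0.85 gives 233 in total.
- SD 1.2, 95% interval: (1.960 + 1.282)² × 2 × 1.44 / 0.25 = 121.1, so 122 per group; 244 / 0.85 gives 288 in total.

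**The case against.** The calculation contains no arithmetic error. The 90% is openly conditional on SD 0.8, and the full range stands in the same paragraph. That is correct, and the point is about the choice of planning value and how widely the 90% is claimed.

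The strongest counter-argument is the blinded re-estimation at 30 per group, which exists to catch an SD larger than planned. The plan also calls 104 a minimum. This stands in part: the low figures describe the initial sample size if it is not increased. It is not a complete answer, because the text leaves open which domain's SD decides whether an increase is needed. A recalculation on a domain with SD 0.8 would confirm 104 while a domain with SD 1.2 stayed at 62%. A reader might infer that the smallest SD will be used again. The document does not say so, and its reference to outcome variables in the plural leans, if anything, the other way. The full protocol may settle the matter.

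A reader might also infer that the trial has 50% to 62% power for its noisier domains as a group. The document does not support that. Both figures belong to the single extreme of SD 1.2, under two different error rates, and nothing shows how many domains lie near it. The 50% also depends on judging by a 95% interval a trial sized at one-sided 5%. That mismatch is separate and lowers power to 83% even at SD 0.8.

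Finally, the document does not say whether 0.8 to 1.2 refers to follow-up or change scores. The primary comparison is described on follow-up scores and the non-inferiority rule on change scores, so the SD that applies to each is uncertain.

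**Conclusion.** The point holds as a limit on the stated power. The initial 104 patients deliver 90% at one-sided 5% only for a domain with SD 0.8. Over the plan's own range, power runs from 90% down to 62% at one-sided 5%, and from 83% down to 50% under the 95% interval rule. The part due to the choice of SD alone is the fall from 90% to 62%.

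This rests on 44 evaluable patients per group, a margin of 0.5, a true difference of 0, the SD range applying to the score analysed, and no increase at the re-estimation. It does not show that the trial as finally conducted will be underpowered.

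**What to change.** In the Sample size section, replace the single 90% with the power over the SD range: 62% to 90% at one-sided 5%, and 50% to 83% with the 95% confidence interval. Alternatively, limit the 90% claim explicitly to a domain with SD 0.8. Say whether the range refers to follow-up or change scores. This costs only wording, although the stated power becomes less favourable.

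State also that the blinded re-estimation at 30 per group will not rest on the smallest domain SD alone, and report the power achieved for each domain at the final sample size. Reporting adds no patients. Which SD drives the sizing is a choice for the sponsor and more than a wording change: if the largest SD were used and proved to be 1.2, the total for 90% power would rise from 104 to about 233 at one-sided 5%, or about 288 with the 95% interval. If that is not feasible, the per-domain power statement lets readers see which domains the trial can settle.

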**Methods/Design:**

We will assign patients with moderately severe to severe COPD to either continuous exercise or interval exercise using a stratified randomisation. Patients will follow 12–15 exercise sessions during a comprehensive inpatient respiratory rehabilitation. Primary end point for effectiveness is HRQL as measured by the Chronic Respiratory Questionnaire (CRQ) two weeks after the end of rehabilitation and secondary endpoints include additional clinical outcomes such as functional exercise capacity, other HRQL measures, patients' experience of physical exercise as well as physiological measures of the effects of physical exercise such as cardiopulmonary exercise testing. Including expected drop-outs, we will need 52 patients per group to show differences corresponding to the minimal clinically important difference of the CRQ. Outcome assessors and investigators involved in data analysis will be blinded to group assignment until analyses have been carried out.

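### The 90% power is stated for showing a 0.5-point CRQ difference at one-sided 5%; under the written non-inferiority rule (95% CI excluding a 0.5 deficit), 44 per group give about 83%

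*Protocol article*

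**What the plan says.** The primary objective, at the end of the Background, is to assess whether interval exercise is not inferior to continuous exercise. The Effectiveness section takes as null hypothesis that continuous exercise is better by at least 0.5 CRQ points. It accepts non-inferiority when the 95% confidence interval for the difference in change scores stays within the pre-set boundary. It adds a further possible conclusion: "If the 95% confidence intervals lie outside the boundaries of clinical equivalence we will establish clinical superiority of one exercise protocol". The legend to Figure 3 gives the boundaries as ±0.5; its sentence on non-inferiority is unclear as to sign, so I rely on the hypotheses and rule in the text.

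The Sample size section uses the standard formula for two means and calls 0.5 the size of the desired difference. It states that "A sample size of 44 patients in each group will allow showing a difference of 0.5 in CRQ scores between the groups". The SD behind this claim is 0.8, the power is given as 90%, and the test level is one-sided 5%. On attrition it says: "Assuming a drop out rate of 15%.[27], the total minimal sample size increases to 104". A parallel sentence claims 95% power, one-sided 5%, to detect 45 metres in the six-minute walk test. The abstract says that "we will need 52 patients per group to show differences corresponding to the minimal clinically important difference of the CRQ".

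The section does not mention non-inferiority, an assumed true difference, or the 95% interval that decides the result.

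**The concern.** In a non-inferiority trial, 0.5 is the deficit to be excluded, and power is the chance of excluding it under an assumed truth, usually no difference. Power to show a difference of 0.5 is the chance of rejecting zero when the truth is 0.5. For a given alpha the two calculations give the same n, so the wording hides which one is meant. The alpha also differs: one-sided 5% in the sample size, but one-sided 2.5% in the tail of a 95% interval that faces the margin.

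Three things follow. The stated 90% is higher than the primary rule delivers. A reader cannot see how quickly power falls if interval exercise is slightly worse, because the zero-difference assumption is not stated. And the recalculation planned at 30 patients per group has no unambiguous target: the article fixes neither the assumed true difference nor an alpha that agrees with the analysis.

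**Working it through.** **Inputs.** Sample size section: margin or difference 0.5; SD 0.8 (from a reported range, "standard deviation of the CRQ domain scores between 0.8 and 1.2"); one-sided alpha 5%; power 90%; equal groups ("n = the sample size required in each group (double for total sample"); dropout 15%. Effectiveness section: 95% confidence interval against a boundary of 0.5. Normal approximation throughout.

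**1. Reproduce the plan's figure.** n = (A + B)² × 2 × SD² / DIFF², with A = 1.645 and B = 1.282:

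(2.927)² × 2 × 0.64 / 0.25 = 8.564 × 5.12 = 43.8, so 44 per group. Dropout: 44 / 0.85 = 51.8, so 52 per group and 104 in total. Both figures reproduce.

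The same formula gives 44 for a non-inferiority test with margin 0.5, true difference 0 and one-sided 5%.

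**2. Apply the written rule.** SE = 0.8 × √(2/44) = 0.1706. The rule succeeds with probability Φ((0.5 − deficit)/SE − z), where z = 1.960 for a 95% interval and 1.645 for a one-sided 5% test.

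| True deficit of interval exercise | 95% CI, as written | One-sided 5%, as in the sample size |
|---|---|---|
| 0 | Φ(2.931 − 1.960) = 83.4% | Φ(2.931 − 1.645) = 90.1% |
| 0.1 | Φ(2.345 − 1.960) = 65% | 76% |
| 0.2 | Φ(1.759 − 1.960) = 42% | 55% |
| 0.5 | Φ(−1.960) = 2.5% | 5% |

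With the noncentral t distribution, the 83.4% becomes 82.6%.

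**3. Size needed for 90% under the 95% interval.** (1.960 + 1.282)² × 5.12 = 10.51 × 5.12 = 53.8, so 54 per group. With dropout, 54 / 0.85 = 63.5, so 64 per group and 128 in total. The ratio 10.51 / 8.564 = 1.23 does not depend on the SD, so the recalculated size will also differ by about 23% according to which alpha is used.

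**4. Sensitivity to the SD.** Under the written rule, with true difference 0 and 44 per group, power is 83.4% at SD 0.8, 65.0% at SD 1.0 and 49.8% at SD 1.2.

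**5. Walk test.** The article gives no SD, so n cannot be checked. Taking the stated 95% at one-sided 5% as exact, margin/SE = 1.645 + 1.645 = 3.290. Under a 95% interval, with no true difference, power is then Φ(3.290 − 1.960) = Φ(1.330) = about 91%.

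**6. Clinical superiority rule.** For the whole 95% interval to lie beyond 0.5 with 90% probability, the true difference must be 0.5 + (1.960 + 1.282) × 0.1706 = 1.05 points.

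**The case against.** The strongest reply is that this is loose wording in a condensed article. The 0.5 in the sample size is the same minimal important difference that serves as the equivalence boundary, and a one-sided alpha fits non-inferiority. Read that way, 44 per group is right and only the zero-difference assumption is unstated. The reading is reasonable, and I accept that the arithmetic is sound. It does not remove the alpha mismatch: the same article specifies a 95% interval for the decision, and Figure 3 places both ends of the interval against ±0.5, so the interval is two-sided.

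A second reply is that the Effectiveness section also plans a t-test between groups, for which showing a difference is natural wording. That test is not the non-inferiority criterion. At two-sided 5% it too has about 83% power at a true difference of 0.5.

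A reader might go further and set the 90% against the clinical superiority rule, noting that at a true difference of exactly 0.5 this rule succeeds only 2.5% of the time. The documents do not support that as a fault in the sample size. A truth placed on the boundary gives 2.5% at any n and any SD; superiority is a further interpretation of the interval; and no power is claimed for it. If interval exercise were truly 0.5 better, the non-inferiority rule would succeed almost always. Only a note that the trial is not sized for the superiority conclusion is warranted.

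**Conclusion.** The point holds: the stated power does not belong to the rule that decides the trial. The primary decision has about 83% power rather than 90%, and this falls to 65% and 42% at true deficits of 0.1 and 0.2 points. These figures assume 44 evaluable patients per group, SD 0.8 for the score on which the interval is built, and the normal approximation. A larger SD within the article's own range lowers them.

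A reader might infer that 44 per group, or 104 in total, was miscalculated. It was not: both reproduce from the stated inputs. The defect is in what the number is said to achieve and at which alpha.

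**What to change.** Reword the power statement in the abstract and the Sample size section in one of two ways:

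- **Keep the 95% interval.** State that 44 evaluable patients per group give about 83% power for the 95% confidence interval to exclude a CRQ deficit of 0.5 for interval exercise, assuming no true difference and an SD of 0.8.
- **Keep 90%.** State the same margin, assumption and SD, and say in the Effectiveness section that non-inferiority is judged by a one-sided 95% bound (equivalently, a two-sided 90% interval).

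Apply the chosen interval level and the zero-difference assumption to the 45-metre walk-test sentence, with 45 metres as its margin. Fix the margin, assumed difference, alpha and target power for the recalculation at 30 per group before it is done. Add one sentence saying that the trial is not sized for the clinical superiority conclusion, which would need a true difference of about 1.05 points for 90% power.

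The cost is wording only, with no change in sample size. The first option makes the stated capability less favourable; the second accepts a one-sided 5% error rate for non-inferiority. Restoring 90% under the 95% interval would be a separate choice, costing 54 per group before dropout (128 in total after it).

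### The sample size is set at one-sided 5% but non-inferiority is decided on a 95% confidence interval (one-sided 2.5%), so at SD 0.8 the planned 44 per arm give about 83% power, not 90%

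*Protocol article*

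**What the plan says.** All references are to the protocol article.

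- **Sample size, CRQ.** The formula is n = (A + B)² × 2 × SD² / DIFF². It yields 44 evaluable patients per arm for a CRQ difference of 0.5. The remaining inputs behind that number are given as "assuming a standard deviation of 0.8, with a power of 90% at a significance level of 5% (one-sided"). An earlier trial by the same group is cited for a "standard deviation of the CRQ domain scores between 0.8 and 1.2"; the calculation takes the lowest value. After 15% drop-out, "the total minimal sample size increases to 104".
- **Sample size, walk test.** The same number is said to detect 45 metres "with a power of 95% at a significance level of 5% (one-sided) assuming a drop out rate of 15"%. No SD for the walk test is given.
- **Effectiveness, decision rule.** The criterion opens with "We will establish non-inferiority of interval exercise if the point estimate and its 95% confidence interval for difference between the change scores"; both must fall below the predetermined boundary. Superiority of either protocol is to be declared if the interval lies outside the boundaries.
- **Effectiveness, Figure 3 legend.** The boundaries are ±0.5 CRQ points, and equivalence is declared when the whole interval lies between them.
- **Sample size, recalculation.** Once 30 patients per group have data, the SD is re-assessed and the sample size adjusted if needed.

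**The concern.** The two sections describe different tests. The words two-sided do not appear next to the 95% interval. However, the interval is held against both ±0.5 boundaries and can show superiority of either protocol, so it is two-sided in use. Requiring one of its limits to clear the margin is a one-sided 2.5% test (z = 1.96). A one-sided 5% test (z = 1.645) corresponds to a two-sided 90% interval or a one-sided 95% bound, and the article specifies neither.

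At stake is the power of the primary objective. At the planned number and SD, the chance of missing true non-inferiority would be about 17% instead of 10%. Because the recalculation updates only the SD, the same mismatch would pass into the final sample size.

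**Working it through.** **Inputs.** Sample size section: margin 0.5, SD 0.8 (range 0.8 to 1.2), 44 evaluable per arm, one-sided 5%, power 90%, drop-out 15%. Effectiveness section: 95% interval. Assumption: true difference zero. The article does not state this, but it is implied by putting DIFF equal to the margin.

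**1. The plan's own figure.** (1.645 + 1.2816)² × 2 × 0.64 / 0.25 = 43.85, so 44 per arm. 44 / 0.85 = 51.8, so 52 per arm and 104 in total. All three stated figures reproduce.

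**2. The same formula at the level of the decision rule.** (1.96 + 1.2816)² × 2 × 0.64 / 0.25 = 53.80, so 54 per arm. 54 / 0.85 = 63.5, so 64 per arm and 128 in total. The stated 44 therefore comes from one-sided 5%.

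**3. Power at 44 per arm.** SE = 0.8 × √(2/44) = 0.1706, and 0.5 / 0.1706 = 2.932.

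- One-sided 5%: Φ(2.932 − 1.645) = 90.1%
- 95% interval: Φ(2.932 − 1.96) = Φ(0.972) = 83.4% (82.6% with the t distribution)

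**4. Range over the protocol's SDs and over the number analysed.**

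| SD | Analysed per arm | Power, one-sided 5% | Power, 95% interval |
|---|---|---|---|
| 0.8 | 44 | 90.1% | 83.4% |
| 1.0 | 44 | 75.8% | 65.0% |
| 1.2 | 44 | 62.2% | 49.8% |
| 0.8 | 52 (no drop-out) | 93.9% | 89.0% |

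**5. Effect on the recalculation.** For 90% power, one-sided 5% gives 69 per arm at SD 1.0 and 99 at SD 1.2. The 95% interval needs 85 and 122. In every case the requirement is larger by (3.2416 / 2.9264)² = 1.23.

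**6. Walk test.** The SD is not given, so power at 44 per arm is shown over assumed SDs as Φ(45 / (SD × √(2/44)) − z).

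| Assumed SD | One-sided 5% | 95% interval |
|---|---|---|
| 64.2 m (gives exactly the stated 95%) | 95% | 91% |
| 60 m | 97% | 94% |
| 55 m | 99% | 97% |

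**7. Equivalence, a separate claim.** With the 95% interval at 44 per arm, SD 0.8 and true difference zero: 2 × 0.834 − 1 = 67%. With a 90% interval: 2 × 0.901 − 1 = 80%.

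**The case against.** The strongest reply is that the error is on the safe side. The 95% interval holds the risk of a false non-inferiority claim at 2.5%, and what is lost is about 7 points of power at SD 0.8. The article itself calls such calculations rough and plans to revisit them, and 44, 52 and 104 are all computed correctly. This stands as a limit on severity: the fault is an inconsistency between two sections, not a slip in arithmetic, and it does not inflate the type I error. It does not remove the point, because the recalculation touches only the SD.

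A second reply is that the drop-out allowance covers the gap. It does so only if nobody drops out, and even then power is 89%.

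Three stronger readings are tempting, and the document does not support them.

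- **That the stated 90% is really 67%.** The 90% was stated for showing a one-sided 0.5 difference, never for equivalence, and the formal hypotheses concern non-inferiority. Equivalence would have only 80% power even with the levels aligned. The missing power for equivalence is a separate note, not a result of this mismatch.
- **That walk-test power is 91%.** That figure requires an SD of about 64 m, obtained by working backwards from the stated 95%. The sample was sized on the CRQ, so 95% may be a rounded or minimum figure.
- **That a baseline-adjusted primary analysis repairs the loss.** At 44 per arm with the 95% interval, and if 0.8 is the SD of follow-up scores, power is Φ(2.932 / √(1 − r²) − 1.96). This gives about 85% at r = 0.2, 87% at 0.3 and 92% at 0.5. The article gives no correlation r and does not say whether 0.8 refers to follow-up or change scores.

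**Conclusion.** The inconsistency is real, and nothing else in the article resolves it. The trial is sized for a one-sided 5% test and decided by a one-sided 2.5% test. With 44 evaluable per arm, SD 0.8 and a true difference of zero, non-inferiority power under the stated rule is about 83%, not 90%. As SD 0.8 is the favourable end of the protocol's range, 83% is not a worst case. The walk-test power is stated at the same one-sided 5% and so does not carry over to a 95% interval, but the document does not allow the size of the loss to be fixed.

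**What to change.** Use one level in the Sample size and Effectiveness sections. Either route reconciles them.

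- **Keep the 95% interval.** Restate non-inferiority power as about 83% at 44 evaluable per arm and SD 0.8, show the values at SD 1.0 and 1.2 beside it, and use z = 1.96 in the recalculation at 30 per group. The cost is a less favourable stated power. Holding 90% instead would need 54 evaluable and 64 randomised per arm, 128 in total against 104.
- **Judge non-inferiority on a two-sided 90% (one-sided 95%) interval.** The 44 per arm support this at SD 0.8. The cost is a 5% risk, rather than 2.5%, of a false non-inferiority claim. The text should then say which interval serves the equivalence and superiority claims.

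Under either route, recompute the walk-test power at the chosen level from the sponsor's own SD, and state that SD. As a separate addition, give the power for the equivalence claim (about 67% with the 95% interval at 44 per arm and SD 0.8), or say that the trial is not powered for it. Making the baseline-adjusted analysis primary is a separate design choice. If it is taken up, the assumed correlation and the type of SD should be stated.

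The change should be made before the recalculation is run; otherwise the mismatch is built into the final sample size.
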